#### Secondary outcomes

Changes in glucose (2 hour OGTT), fasting lipids, blood pressure, depression, quality of life, physical activity and diet are the secondary outcome, which will be assessed at baseline and 12 months for all women.

### Anthropometric measurements and laboratory testing

To ensure that the clinical measurements meet research standards, measurements will be carried out by specially trained study nurses/phlebotomist. All clinical tests will follow the latest international recommendations from the European Health Risk Monitoring protocol [27]. Blood samples will be collected by the study nurse/phlebotomist, and analyzed by Melbourne Pathology (Victoria) or ClinPath (South Australia). Anthropometric measurements including height, weight, waist and hip circumference, and blood pressure will be taken. Women will be asked to fast from 10 pm the night before their appointment and venous samples will be drawn at the appointment to analyze lipids (triglycerides, total cholesterol, low-density lipoprotein and high-density lipoprotein cholesterol), HbA1c and glucose (fasting and 2 hour OGTT). Additional blood from women who consent to having their blood stored will be bio-banked at −80°C for further additional analyses.

For the intervention group only, at three months after baseline testing or as soon as possible after the final group session, a follow-up assessment will repeat all blood tests (except OGTT), and anthropometric measurements of weight and waist circumference. All women who complete this clinical testing will receive a standardized feedback letter documenting their results and any evidence of high blood pressure or depression. A copy will be sent to their nominated GP.

#### Self-report measures

Women will be asked to complete a comprehensive survey that includes demographic questions (at baseline only); measures of health behavior including the Food Frequency Questionnaire [28], the Active Australia Questionnaire [29], self-regulation [30] and self-efficacy for diet and physical activity [23,24,31,32]; social support (Multidimensional Scale of Perceived Social Support [33]); quality of life (Assessment of Quality of Life, AQoL-8D) [34]; depression and suicidal ideation (Patient Health Questionnaire 9, PHQ9 [35]); and health status questions (including demographics, smoking status, and history of diabetes, myocardial infarction, cancer, and mental disorders) at baseline and 12 months post-baseline.

If a woman scores 11 points or more on the PHQ9 and/or if she scores on the suicidal-ideation question (question 9), this result will be discussed with her at the time to establish whether she is aware of her depression risk, and she will be advised to attend her GP for further discussion and management. This will also be highlighted in the results feedback letter to the woman and her GP.

A healthcare resource use cost diary will be given to all women to record utilization of diabetes-related healthcare services during the time from baseline to completion of the study. The diary aims to collect costs associated with activities related to GDM follow-up (such as weight management and measurement of blood pressure, glucose and lipid), and will include healthcare, time, and travel costs. An additional purpose of the diary is to determine any differences between the intervention and control groups in seeking advice about lifestyle change and diabetes prevention.

### Sample size and power calculation

For the estimation of sample size for two groups, using a two-sided 5% significance level and 80% power, the total number required will be 430 (215 in each arm). The sample size calculation was based on the observed mean change in FPG over 12 months in the Greater Green Triangle Diabetes Prevention Program (GGT DPP) study [36] and is powered to detect an effect size of 0.27 (assuming mean difference between intervention and control groups of 0.14 mmol/L and within group standard deviation of 0.5 mmol/L). To allow for an estimated attrition rate of up to 25% (estimate based on the GGT DPP), we will require a total sample of 574 (287 in each arm). This sample size will provide sufficient power to also analyze changes in weight and waist circumference. The intention-to-treat (ITT) principle will be adhered to, and sensitivity analysis will also be carried out.

### Data collection

Participants’ blood test results will be uploaded onto the Melbourne Pathology/ClinPath websites, which are password-encrypted. In order to protect confidentiality, the participant ID number and date of birth will be the only identifying information available to the laboratory. Melbourne Pathology will also post hard copies of the pathology results to the study office (Deakin University), and ClinPath will send their hard copy results to the study office in South Australia in secure envelopes via ClinPath couriers.

Web-based survey forms will be used primarily to collect information during the testing appointment, with the paper-based system used as a back-up. Clinical measurements will be recorded by the study nurse. All questionnaires are self-reported by the participating women, and will use the participant ID number (on the front of each form/questionnaire) as the identifier. Only the demographic questionnaire contains the participants’ contact details, and this will be maintained separately from all of the other information relating to each woman.

### Data storage and management

All data will be stored on Deakin University eSolutions servers (ISO 9000 compliant for security, access and quality control) and the National eResearch Collaboration Tools and Resources (NeCTAR) server. Data collected by the research team will be transferred to locked cabinets at the respective study offices, and 10% of hard copy questionnaires will be randomly audited for quality control.

### Data analysis

Analyses will be performed using STATA version 12 or later (Stata Corp., College Station, TX, USA) and the ITT principle will be adhered to. Baseline characteristics will be compared between the intervention and control groups using χ^2^ tests, independent t-tests, and/or the Wilcoxon rank-sum test, as appropriate. Primary and secondary outcome (as described above) will be evaluated using mixed models, treating ‘group’ as a between-subject factor, and ‘time’ as a within-subject factor. Two-sided tests will be used, with a level of *P*<0.05 determining statistical significance.

A separate and parallel economic evaluation protocol will be described elsewhere.

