### Randomization

Block randomization will be implemented and separate randomization lists for each ‘venue’ or ‘stratum’ will be created. Each list will be supplied as a separate file and will be imported into the current MAGDA management database, which selects the next available sequence number for the venue/stratum. This sequence number will be displayed, along with the assignment code (control or intervention) to the user in the randomization office at Deakin University.

Women will be randomized into either the intervention or control arm after the baseline blood results have been received by the MAGDA-DPP project manager. If the woman does not have diabetes, the project manager or senior program manager will randomize her using the MAGDA-DPP management database. Each woman will receive a letter with the outcome of her randomization along with her baseline test results, and a copy will be sent to her nominated GP.

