#### Primary outcome

The primary outcome is the change in diabetes risk, as determined by changes in FPG, weight, or waist circumference. A statistically significant change in any one of these three endpoints will be regarded as evidence of a change in diabetes risk. No adjustments to significance levels will be made for multiple testing. These co-primary outcome will be assessed at baseline and 12 months for all women, and additionally at 3 months (or as soon as possible after the final group session) for the intervention participants only.

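### Read naturally, the group-by-time mixed model leaves baseline means free in each arm; it is valid, but less precise than a baseline-adjusted 12-month comparison that uses data already collected

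*Protocol article*

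**What the plan says.** The Data analysis section states that primary and secondary outcomes "will be evaluated using mixed models, treating ‘group’ as a between-subject factor, and ‘time’ as a within-subject factor". It names no baseline covariate, no common-baseline constraint and no particular model term as the test of the intervention.

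The Primary outcome section sets the scale: "The primary outcome is the change in diabetes risk, as determined by changes in FPG, weight, or waist circumference". These measures "will be assessed at baseline and 12 months for all women, and additionally at 3 months", the 3-month visit being for the intervention arm only. Baseline and 12 months are thus the only times common to both arms.

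The Randomization section fixes the order of events: "Women will be randomized into either the intervention or control arm after the baseline blood results have been received". The Consent section likewise places baseline data collection ahead of allocation, which covers weight and waist as well as fasting plasma glucose (FPG).

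The Sample size section is "based on the observed mean change in FPG over 12 months" in an earlier programme and is "powered to detect an effect size of 0.27". It asks for 215 evaluable women per arm, raised to 287 per arm for attrition of up to 25%.

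**The concern.** If baseline is a level of the time factor, it is treated as a response, and a group factor lets its mean differ between arms. The term that targets a difference in change is then the group-by-time interaction. With complete data at two visits, this is simply the difference in mean change.

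In a randomised trial with baseline taken before allocation, a true baseline difference between arms is known to be zero. A model that estimates it anyway gives up information, and the whole of any chance baseline difference is subtracted from the 12-month difference, whatever the correlation between visits. Constraining the baseline means to be equal, or regressing the 12-month value on baseline, subtracts only the share that the correlation supports. What is at stake is the width of the confidence intervals for FPG, weight and waist, and some power.

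**Working it through.** **Inputs.** From the article: two-sided 5% level, 80% power, effect size 0.27, 215 evaluable and 287 randomised per arm, 25% attrition. Assumed, because the article does not give them:

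- rho, the correlation between baseline and 12-month values, shown over a range;
- equal SDs at the two visits;
- 12-month values missing completely at random;
- 0.27 is on the scale of the change score.

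**The plan's own figure.** n per arm = 2 × ((1.960 + 0.842)/0.27)² = 215.3, which matches the stated 215. Power at 215 per arm is 79.9%. 430/0.75 = 573.3, hence 574. The sample size is reproduced. (The quoted difference and SD give 0.14/0.5 = 0.28, which would need 201 per arm; the stated number follows 0.27.)

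**Identity with the change score.** In one simulated complete two-visit data set, the group-by-time coefficient and the difference in mean change agreed (−0.0261 for both, SE 0.1020 for both).

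**Variances per arm.** Let s be the SD at one visit, m the number evaluable at 12 months and n the number randomised, with m/n = 0.75.

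- Change score in completers: 2s²(1 − rho)/m.
- Free-baseline mixed model, which also uses the baselines of women who drop out: s²[(1 − rho²) + 0.75(1 − rho)²]/m. Divided by the change-score variance, this is (1.75 + 0.25 rho)/2.
- Common-baseline or baseline-adjusted model: s²(1 − rho²)/m. Divided by the change-score variance, this is (1 + rho)/2.
- Adjusted against free-baseline: 1/(1 + 0.75(1 − rho)/(1 + rho)).

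**Power.** Power = Φ(0.27 × √(215/2)/√F − 1.96), where F is the variance factor relative to the change score and 0.27 × √(215/2) = 2.799.

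| rho (assumed) | F, free baseline | Power, free baseline | F, adjusted | Power, adjusted | Variance ratio, adjusted to free |
|---|---|---|---|---|---|
| 0.5 | 0.9375 | Φ(2.891 − 1.96) = 82.4% | 0.750 | Φ(3.232 − 1.96) = 89.8% | 0.80 |
| 0.7 | 0.9625 | Φ(2.853 − 1.96) = 81.4% | 0.850 | Φ(3.036 − 1.96) = 85.9% | 0.88 |
| 0.9 | 0.9875 | Φ(2.817 − 1.96) = 80.4% | 0.950 | Φ(2.872 − 1.96) = 81.9% | 0.96 |
| 0.95 | 0.9938 | Φ(2.808 − 1.96) = 80.2% | 0.975 | Φ(2.835 − 1.96) = 80.9% | 0.98 |

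The gain is about 7, 4.5, 1.5 and 0.7 percentage points.

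**Simulation check.** In 6,000 simulated trials per value of rho, with 287 per arm and 215 observed at 12 months, closed-form versions of the estimators gave adjusted-to-free variance ratios of 0.82, 0.88 and 0.97 at rho 0.5, 0.7 and 0.9. The mean estimated effect was about −0.27 for every estimator, so none was biased.

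**If the SD of 0.5 is that of a single value.** The article does not say which SD it is. The variance ratios do not change, but the absolute numbers do. With difference 0.14 and complete data, n per arm for 80% power is 281 (change score) against 183 (adjusted) at rho 0.3, 201 against 151 at 0.5, and 121 against 103 at 0.7.

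**The case against.** The strongest objection is that the article does not write the free-baseline model out. It names two factors; a common-baseline model has the same two factors, and parameterisation is often left to a statistical analysis plan, which is not shown here. That stands as a limit on certainty: the free-baseline form is the natural reading, not a quoted one. It does not remove the point, because the article does name its method, and a better one is available from the trial's own design.

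A second objection is that the plan is coherent as it is: the outcome, the sample size and a group-by-time test all concern change. That also stands. Several stronger readings that a reader might infer are not supported:

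- **Bias or an inflated type I error.** Chance baseline imbalance is ordinary sampling variation and is already in the standard error. The loss is precision only.
- **The planned model is exactly a change-score analysis.** That holds only for complete two-visit data. With 25% attrition the likelihood also uses dropouts' baselines, and the intervention-only 3-month values can shift the estimate.
- **A gain counted from 80%.** That figure belongs to a completer change-score test with 215 per arm. The free-baseline model with 287 randomised per arm starts slightly higher, so the gain at rho 0.5 is about 7 points, not 10.
- **A group main effect as the test**, which would average a null baseline with 12 months and dilute the effect. Nothing in the article suggests this; it defines the outcome as change and includes time as a factor.

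**Conclusion.** The point holds as a modest efficiency improvement. On its natural reading, the stated model gives a valid, unbiased comparison that is less precise than one using the pre-randomisation baseline properly. Against the free-baseline model with 25% missing, the variance falls by about 20% at rho 0.5, 12% at 0.7, 4% at 0.9 and 2% at 0.95.

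These sizes rest on an assumed rho, equal SDs at both visits, losses completely at random and, for the power figures, 0.27 being on the change scale. No rho is given for any endpoint. If weight and waist correlate at 0.9 or above over 12 months, the benefit for them is slight; it would be larger for FPG if FPG correlates less strongly. The planned numbers of 430 evaluable and 574 randomised need no revision on this account.

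**What to change.** State in the Data analysis section that each primary outcome will be analysed by a mixed model with one baseline mean common to both arms, or by a regression of the 12-month value on arm and baseline value. Name the arm difference at 12 months as the primary contrast for FPG, weight and waist. The two options are close but not identical once 3-month values enter the mixed model, so one should be chosen, and the text should say whether the intervention-only 3-month values are used.

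The cost is a sentence or two and about one degree of freedom, with no new data, visits or participants. On the article's own dates, baseline testing began in July 2012 and 134 women had been randomised by 4 June 2013, so no 12-month visit was yet due and the choice could still be fixed before outcome data. If an analysis plan already includes a baseline term, the published text need only be aligned with it.

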## Discussion

Gestational diabetes mellitus is the strongest single population predictor of T2DM. At least 20 to 50% of women who have GDM will go on to develop diabetes within 28 years [8,37], and women with GDM have a life-time risk exceeding 70% of developing T2DM [4]. Lifestyle-modification programs are effective in delaying or preventing diabetes in the general high-risk population. Although there were some post-GDM women in the US DPP [7], no intervention program has previously been specifically designed and tested for this group.

This study is necessary because it is important to know if the MAGDA-DPP intervention leads to a reduction in diabetes risk in women with a history of GDM. Defining the participants’ characteristics that predict attendance and completion of the intervention and improvement in clinical and behavioral measures will be useful for further development of DPPs for this population in Australia and internationally.

### Trial status

Recruitment in Melbourne (Victoria) commenced at The Royal Women’s Hospital in January 2011, followed by Sunshine Hospital in November 2011 and in Adelaide (South Australia) at Lyell McEwin Hospital in January 2012. By June 4, 2013, 1,517 women diagnosed with GDM have been approached during their clinic appointments at the above three hospitals. Of these, 340 women have given written consent, 219 have not yet returned their consent form, 701 have declined to participate in the study and 257 were ineligible. Recruitment, both retrospectively and prospectively, at Women’s and Children’s Hospital and Flinders Medical Centre in Adelaide is expected to commence in mid-2013.

Baseline testing commenced in July 2012 in Melbourne (Victoria) and March 2013 in Adelaide (South Australia). By June 4, 2013, 134 women had been randomized to either the intervention or the control group. The first MAGDA-DPP intervention group started in November 2012, and there have been six groups, four in Melbourne (Victoria) and two in Adelaide (South Australia), initiated since then.

## Abbreviations

AQoL-8D: Assessment of quality of life; DPP: Diabetes prevention program; FPG: Fasting plasma glucose; GCT: Glucose challenge test; GDM: Gestational diabetes mellitus; GGT DPP: Greater green triangle diabetes prevention program; GP: General practitioner; HAPA: Health action process approach; IDAPSG: International diabetes association of diabetes and pregnancy study groups; MAGDA-DPP: Mothers after gestational diabetes in Australia diabetes prevention program; NDSS: National diabetes services scheme; NeCTAR: National eResearch collaboration tools and resources; NHMRC: National health and medical research council of Australia; OGTT: Oral glucose tolerance test; PHQ9: Patient health questionnaire; PI&CF: Participant information and consent form; SA: South Australia; T2DM: Type 2 diabetes mellitus; VIC: Victoria.
